**Protocol 2 (12/04/2019):**

**Protocol:** The development of nutritional biomarker scores as indicators of dietary quality assessed by predefined dietary patterns, and evaluation of their association with and predictive ability for type 2 diabetes incidence

**Proposer**: [name]

**Affiliation**: MRC Epidemiology Unit

**Working group participants**: [name], [name], [name], [name], [name], [name]

**Research question:** Nutritional biomarkers have been used to measure nutrient intake or status primarily on single biomarker-single nutrient basis. The use of multiple circulating biomarkers to assess overall dietary quality is rarely evaluated. Thus, we hypothesise that concurrent use of a wide range of biomarkers could reflect levels a specific dietary pattern. The expected increase in precision of capturing dietary exposure would increase the statistical power to detect diet-disease associations and also enable the evaluation of possible effect-modification of the association by genetic variation in susceptibility to obesity, insulin resistance or T2D. The InterAct study has measured self-reported habitual diet, gene variants, and a variety of nutritional biomarkers including circulating vitamin C, carotenoids, 25(OH)D and phospholipid fatty acids, and nutrition-related biomarkers such as calcium, magnesium and iron status markers. Thus, it provides a unique opportunity to develop nutritional biomarker scores of specific dietary patterns. The association of these scores with incident type 2 diabetes (T2D) could then be evaluated as a means of assessing predictive criterion validity.

**Objectives**

**(1)** To evaluate whether a combination of nutritional biomarker variables could be used to develop biomarker scores predictive of dietary patterns.

**(2)** To evaluate the association of the biomarker scores with T2D incidence.

**(3)** To evaluate the predictive ability of the biomarker scores for T2D incidence.

**Main exposures:**

1. Nutritional biomarker score(s) developed by using circulating vitamin C, carotenoids (α-carotene, β-carotene, β-cryptoxanthin, lycopene, lutein, zeaxanthin), and phospholipid fatty acids (individual and groups of fatty acids to include marine n-3 fatty acids [EPA+DHA+DPA], ALA, LA (n-6 PUFA), odd-chain SFA, even-chain SFA, very-long-chain SFA, MUFA and trans fatty acids). We will also include nutrition-related biomarkers: circulating 25(OH)D, 25(OH)D_3_-epimer (D_2_ and D_3_-non-epimer will not be used due to high rates of missing data [6]), magnesium, calcium, and iron status markers. As specified in the analysis of individual fatty acids [7], fatty acids with concentrations < 0.05 mol% will not be used.

2. Self-reported dietary factors including major food groups and predefined dietary patterns [Mediterranean diet score (MDS), Dietary Approaches to Stop Hypertension (DASH), Alternative-Healthy Eating Index 2010 (aHEI)].

**Main potential confounding factors:**

**1. Association of biomarkers with dietary pattern scores:** Country, centre, age, sex, BMI, waist circumference, education, physical activity, smoking status, medication use, season of blood draw, total cholesterol (in relation to concentrations of carotenoids).

**2. Prospective associations of biomarker scores with incident T2D:** Country, centre, age, sex, BMI, waist circumference, smoking status, alcohol intake, education, physical activity, medical history (cancer, CHD, stroke), family history of diabetes, lipid-lowering medication, month of blood collection, dietary factors (total energy intake, other nutritional factors not included in calculations of respective dietary pattern indices will be considered), and in women, menopausal status and hormonal preparations use. We will also consider metabolic markers, i.e. markers of lipids (total cholesterol, HDL-cholesterol, LDL-cholesterol, triglycerides), inflammation (CRP), hepatic function (ALT, AST, GGT), and glycaemia (HbA1c, particularly to exclude those with raised HbA1c>48mmol/mol (or >6.5%). Final choice of covariates will be made with the goal of maximizing precision of the estimate for the main exposure without inducing a meaningful change in the estimate (>5% comparing models with and without a given covariate).

**Analysis Plan**

**Exclusions:** For the development of biomarker scores, we will restrict the analysis to the subcohort without missing data on nutritional biomarkers. Furthermore, EPIC-Oxford participants recruited via postal methods purposely oversampling vegetarians will be excluded in the primary analysis, and included as sensitivity analysis. Other exclusions will encompass: missing dietary data required for calculating dietary pattern indices; estimated daily energy intakes less than 800 kcal or more than 4,000 kcal for men and less than 500 kcal or more than 3500 kcal for women; prevalent cardiovascular disease or cancer, ferritin levels higher than 1,000 μg/L. Fatty acids with a mean concentration < 0.05% in the subcohort will not be used in the analyses.

For prospective associations of biomarker scores with T2D, participants with prevalent diabetes will be excluded.

**Descriptive statistics:** Descriptive statistics will be presented separately for each country. Measures of central tendency and dispersion or frequencies will be used, as appropriate, to describe sociodemographic and lifestyle characteristics, anthropometry, medical history, concentrations of (non-nutritional) metabolic markers, and concentrations of nutritional biomarkers included in the scores. These characteristics will also be presented within categories of adherence to dietary patterns, e.g. by quintiles.

**Biomarker scores derivation**: Food and nutrient intakes required for calculating dietary pattern scores will be estimated from food frequency questionnaires or diet histories (FFQ). Dietary pattern components with data unavailable in EPIC-InterAct will be excluded from score calculations (sodium for DASH and aHEI, trans-fatty acids for aHEI). Dietary pattern scores will be treated as continuous variables. Additionally, we will calibrate the intakes estimated from the FFQ against the 24h recalls (24-HR) administered in a random subset of the EPIC cohort using the following formula:

FFQ’ = 24-HR_mean_ + λ(FFQ – FFQ_mean_),

where 24-HR_mean_ and FFQ_mean_ denote population mean intake levels estimated by the two methods, and λ denotes the calibration factor. This factor represents the slope of the regression line obtained from linear regression of FFQ-estimated intake on the corresponding intake estimated from 24-HR [8,9]. Remaining analyses outlined below will be conducted both using uncalibrated and calibrated data, and the latter will be treated as secondary analyses as only a single 24-HR is available.

Biomarkers with highly right-skewed distributions will be log-transformed. Seasonality in 25(OH)D concentrations will be addressed by using a linear combination of sine and cosine functions of day of the year of blood draw. Carotenoids will be entered into the prediction models as residuals from linear regression models of individual carotenoids’ concentrations on total serum cholesterol concentrations. Concentrations of plasma fatty acids will be expressed as mole percentages.

Elastic net regression will be used to derive the biomarker scores in order to address collinearity between biomarkers and decrease data over-fitting in derivation datasets. Other regularization methods may also be considered. Because such methods account for linear combinations of predictors, we will evaluate potential non-linear associations between biomarkers and dietary patterns. In order to minimise the risk of data overfitting, we will use only restricted cubic splines with few knots. Similarly, we will undertake exploratory analyses to test all the possible first-order interaction terms simultaneously to verify the assumption of no interaction in a common prediction algorithm. Given the relative novelty of the topic of developing nutritional biomarker scores, we will also allow for other exploratory analyses or post-hoc analyses as indicated by results of the pre-specified analyses. If needed, such additional analyses will be agreed upon by the Working Group members and introduced as amendments to the statistical analysis plan prior to conducting them.

Considering goodness to fit and parsimony of a model, we will identify regression models to derive the biomarker scores, assign regression coefficients as weights to individuals’ data, and sum up the resulting products as a biomarker score. Performance of the equations will be assessed in the validation datasets by applying linear regression (non-penalized) and calculating R^2^. In order to assess whether personal characteristics identified in the literature as determinants of dietary misreporting (age, sex, BMI, and educational attainment) or factors influencing concentrations of some nutritional biomarkers (age, BMI, physical activity, smoking status, alcohol intake, medication use, season of blood draw) improve proportion of variance explained in adherence to dietary patterns, we will further include these factors in an additional model and calculate gains in R^2^. A backward deletion procedure at *P*-value = 0.10 will be applied to eliminate non-influential personal characteristics.

We will take at least two approaches to assess population-specific average internal validity and multi-national validity. For both types of validity, we will use an iterative procedure of developing the regression equations for biomarker scores in all but one study centre within country (internal validity) or country (multi-national validity) and testing their performance in the remaining study centre or country, respectively (validation dataset). However, the performance of the biomarker scores may vary among different population subgroups, and this approach may misrepresent performance of the biomarker scores. Thus, we will also assess validity by means of random splitting of the data. To aid interpretation of the results and potential differences between the two approaches, we will assess similarity between the study centres within countries, as well as between whole-country cohorts, with regards to dietary intakes, and sociodemographic and phenotypic characteristics of the participants.

Correlation coefficients between the biomarker scores and intakes of foods or nutrients used in calculations of dietary pattern adherence scores will be estimated.

**Prospective associations of the biomarker score with T2D:** Associations between the biomarker scores and incident T2D will be examined using multivariable adjusted, Prentice-weighted Cox regression. Country-specific estimates will be calculated, and pooled via random effects meta-analysis with stratification by discovery and validation datasets. We will assess departure from linearity using restricted cubic splines with the number of knots determined by the Akaike information criterion. As a complementary strategy to presenting Hazard Ratios, longitudinal results, T2D-free time from 50 years of age will be estimated across different degrees of the biomarker score.

We will fit the following models, with continuous covariates modelled using linear terms (in case of no evidence of departure from linearity) or restricted cubic splines (if non-linearity is detected or expected a priori, e.g. BMI):

Model 1 – adjusted for age, centre, sex, physical activity, smoking status, education level, total energy intake, alcohol.

Model 2 – as for model 1, plus BMI

Model 3 – as for model 2, plus dietary factors

Model 4 – as for model 3, plus metabolic factors

Analyses will be conducted using multiply-imputed, singly-imputed and non-imputed datasets (complete case-analysis) [10], depending on the degree and patterns of missing information. Multiple imputation will be applied to missing data in relation to covariates, as well as components of the biomarker score(s) at the stage of developing regression equations for calculating the score(s). Final values of the score(s) will not be directly imputed. We will undertake sensitivity analyses comparing the results between multiple imputation, single imputation, and complete-case analyses.

We will evaluate interactions by genetic risk scores for BMI, insulin resistance, T2D; age, sex and BMI. The list may be expanded with further identification of biologically plausible effect modifiers. Both multiplicative and additive interaction will be assessed.

Sensitivity analyses:

- Exclusion of participants with raised HbA1c>48mmol/mol (or >6.5%)
- Exclusion of T2D cases occurring in the first two years of follow-up
- Adjustment for foods or nutrients used for calculations of scores of adherence to dietary patterns

**Predictive modelling:** We will take at least two approaches to assess population-specific average internal validity and multi-national (internal-external) validity. Internal validity will be assessed by bootstrapping, rather than the split sample approach, in order to maximize statistical efficiency [11]. For the internal-external validation, we will use an iterative procedure of developing the prediction model in seven countries and validating it in the remaining country [12]. The so-called blow-up approach will be used to extrapolate case-cohort data to approximate T2D incidence.

A basic model will be specified with covariate selection based on established risk factors, i.e.: age, sex, smoking status, adiposity (BMI, waist circumference), physical activity, self-reported cardiometabolic disease, self-reported intakes of selected foods and metabolic markers (HbA1c, CRP, blood lipids, hepatic enzymes). Reproductive factors in females will be considered. The Royston-Sauerbrei’s D statistic will be used to estimate the proportion of variation explained by each model.

Utility of the biomarker score in improving risk prediction will be assessed by comparing gains in discrimination and calibration of models before and after inclusion of the score in the basic model. Use of individual biomarkers or reduced sets of biomarkers (to facilitate potential clinical application) will be considered upon developing the biomarker score(s).

Discrimination will be evaluated using the C-statistic and Net Reclassification Index, and calibration by plotting predicted survival curves against observed Kaplan-Meier curves in the validation dataset, as well as calculating the Brier score. Country-specific estimates and their heterogeneity will be summarised using random-effects meta-analysis. Additionally, subgroup analyses will be undertaken by sex, age (<60 years vs ≥60 years), BMI (<25 kg/m2 vs ≥25 kg/m2), and waist circumference (men <102 cm vs ≥102 cm; women <88 cm vs ≥88 cm).

**Cross-sectional analysis:** We will evaluate cross-sectional associations of the biomarker scores with circulating metabolic factors and anthropometry using linear-regression with adjustment for potential confounders (see Models 1 and 2 above). Given the moderate overlap in the nutritional biomarker panel between EPIC-InterAct and NHANES in years 2003-2006 and 2011-2014 [13], depending on the composition of the biomarker score(s) derived in the current study, corresponding cross-sectional analyses will be conceived among the Working Group members as a means of external validation [14].

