**Title:** Protocols for the manuscript “A nutritional biomarker score of the Mediterranean diet and incident type 2 diabetes: integrated analysis of data from the MedLey randomised controlled trial and the EPIC-InterAct case-cohort study”

**Background:** The statistical analysis plan for this study was covered by two protocol documents written prior to establishing a collaboration between the EPIC-InterAct and MedLey studies. These documents are broader in their scope than the current analysis alone, and not all described analyses or named studies are included in the current manuscript.

**Protocol 1** (Pages 2-5 of this document) describes the joint analysis of the MedLey trial and EPIC-InterAct, for which we planned to use a publicly deposited dataset of the MedLey trial (<https://doi.org/10.3390/nu9060534>). The specific dataset did not include most individual fatty acids, but rather groupings of major fatty acids (e.g., sum of saturated fatty acids).

**Protocol 2** (Pages 6-9) describes an initial idea of the EPIC-InterAct investigators to derive nutritional biomarker scores of the Mediterranean diet and other dietary patterns internally based on prediction of self-reported dietary intakes from concentrations of all nutritional biomarkers measured in the cohort. The description of prospective analyses of associations between the biomarker scores and risk of type 2 diabetes was applied to the current analysis.

**Amendments** (Pages 10-11) describe further analytical and data presentation decisions for the current manuscript undertaken upon establishing a collaboration of EPIC-InterAct with the MedLey trial with full biomarker data sharing.

**References** for all documents are available on Page 12.

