**Amendments (summarised on 18/11/2022):**

1. *Use of raw data of individual fatty acids rather than publicly deposited data of groups of fatty acids*. Following gaining access to full biomarker data in the MedLey trial, EPIC-InterAct investigators reconsidered the “biomarker score of clinical intervention assignment” (Protocol 1) as our primary approach to derivation of a biomarker score of the Mediterranean diet, as reported in the current manuscript. Prior to this, we viewed the use of groupings of fatty acids in the MedLey trial (as available in the publicly deposited dataset) for external application of the biomarker score to EPIC-InterAct as too strong a threat to validity of the analysis to consider this type of biomarker score as our primary approach, because the composition of individual fatty acids within such groupings may have been fundamentally different between the two studies.

2. *Use of logistic elastic-net regression modelling individual biomarkers and their first-order interactions rather than use of standard logistic regression with backwards selection of individual biomarkers*. We increasingly recognised the utility of elastic net regression to develop a model predicting a dependent variable with multiple correlated predictors. We also found the assumption of no interactions between biomarkers in the score to be severely violated and we allowed for selection of predictors among all pairwise biomarker interactions in addition to log-linear terms. Because of the need to consider a pool of predictor variables exceeding the number of participants following this amendment, we applied logistic elastic net regression as our primary method of variable selection in lieu of logistic regression with backwards selection based on minimising the Bayesian information criterion.

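### Protocol 2 defines the FFQ calibration factor λ as the slope of FFQ on 24-HR, the reverse of what its calibration formula needs; only secondary analyses are affected

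*Combined protocol and SAP*

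**What the plan says.** In Protocol 2, Analysis Plan, under biomarker scores derivation, the plan states: "we will calibrate the intakes estimated from the FFQ against the 24h recalls (24-HR) administered in a random subset of the EPIC cohort". The formula given is FFQ′ = mean(24-HR) + λ × (FFQ − mean(FFQ)), where the two means are population means by each method.

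The next sentences define λ as "the slope of the regression line obtained from linear regression of FFQ-estimated intake on the corresponding intake estimated from 24-HR", citing two references. The later analyses are to be run on both uncalibrated and calibrated data, and "the latter will be treated as secondary analyses as only a single 24-HR is available".

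Two other places bear on how far this reaches. The opening Background of the document says of Protocol 2: "The description of prospective analyses of associations between the biomarker scores and risk of type 2 diabetes was applied to the current analysis". Item 1 of the Amendments (summarised on 18/11/2022) takes up the score of randomised assignment in MedLey "as our primary approach to derivation of a biomarker score of the Mediterranean diet, as reported in the current manuscript". No amendment changes the definition of λ.

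**The concern.** The formula takes FFQ as its input and returns a value on the 24-HR scale. The least-squares line that does this has the slope of 24-HR (dependent) on FFQ (independent). The definition names the other regression, and the two slopes agree only when the two variances are equal.

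An analyst who followed the sentence would give calibrated intakes too little or too much spread around a correct mean, by a factor that can differ from food to food. That matters where a dietary score compares an intake with a fixed amount, or combines several intakes that were each calibrated separately. Biomarker scores trained on such dietary scores would inherit the problem.

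**Working it through.** **Inputs.** The formula, the definition of λ and the secondary status of the calibrated analyses come from Protocol 2, biomarker scores derivation. The documents give no value of λ, no SDs and no FFQ/24-HR correlation. There is therefore no stated figure to reproduce, and every SD and correlation below is an assumption.

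**1. How the sentence reads.** The same section uses the ordinary convention, dependent variable first, when it describes carotenoids as "residuals from linear regression models of individual carotenoids’ concentrations on total serum cholesterol concentrations". Read the same way, the definition of λ makes FFQ the dependent variable.

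**2. The two slopes.** Write r for the correlation of FFQ and 24-HR.

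- Needed by the formula: λ = Cov/Var(FFQ) = r × SD(24-HR)/SD(FFQ).
- As defined: λ = Cov/Var(24-HR) = r × SD(FFQ)/SD(24-HR).
- As defined ÷ needed = Var(FFQ)/Var(24-HR). The correlation cancels.

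**3. Size over a range of assumed SD ratios, with r = 0.4 assumed.**

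| SD(24-HR)/SD(FFQ) | λ needed | λ as defined | As defined ÷ needed |
| --- | --- | --- | --- |
| 0.8 | 0.4 × 0.8 = 0.32 | 0.4 / 0.8 = 0.50 | 1.56 |
| 1.0 | 0.40 | 0.40 | 1.00 |
| 1.25 | 0.50 | 0.32 | 0.64 |
| 1.5 | 0.60 | 0.27 | 0.44 |
| 2.0 | 0.80 | 0.20 | 0.25 |

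The error can go either way, and it vanishes when the variances are equal.

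**4. Simulation check (1,000,000 records per scenario, assumed SDs).** A correctly calibrated FFQ′ should give a slope of 1 when 24-HR is regressed on it. With the needed λ the slope was 1.0 in all four scenarios. With λ as defined it was 3.36, 0.84, 0.40 and 10.0, for Var(FFQ)/Var(24-HR) of 0.30, 1.20, 2.50 and 0.10.

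**5. The single recall.** Let 24-HR = T + e, with e independent of true intake T and of FFQ. Then Cov(FFQ, 24-HR) = Cov(FFQ, T) and Var(24-HR) = Var(T) + Var(e). Recall error enters the denominator of the slope as defined but not that of the needed slope. Suppose SD(T) = 20 and FFQ = 20 + 0.7T plus error of SD 20:

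- Cov = 0.7 × 400 = 280, and Var(FFQ) = 0.49 × 400 + 400 = 596.
- Needed λ = 280/596 = 0.47, whatever the recall error.
- As defined, recall error SD 10: 280/(400 + 100) = 0.56.
- As defined, recall error SD 40: 280/(400 + 1,600) = 0.14. The simulated SD of calibrated intake is then 3.4 instead of 11.5.

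**6. What does not change.** The mean of FFQ′ equals mean(24-HR) for any λ. A positive λ preserves the order of individuals within a calibration group.

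**The case against.** The strongest reply accepts the algebra and disputes the reach. Most of it stands.

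- **The main result does not depend on λ.** Each calibrated analysis is secondary and is paired with an uncalibrated one. The primary score is trained on assignment in MedLey and uses no FFQ or 24-HR intake. A reader might infer from a reversed calibration slope that the diabetes result is compromised; the documents do not support that.
- **Not every calibrated intake need be wrong.** The error requires that the sentence be followed literally and that the two variances differ for that food or nutrient.
- **It is not established that the dietary scores would be wrong.** The plan speaks of population means and does not say that λ differs by country or sex. With one positive λ per food, even pooled quantile cut-offs on that food are unchanged. Fixed cut-offs and combined components are exposed, but the plan does not say how each index is scored, or whether calibration comes before or after summing.
- **The plan states no bias concern about the single recall.** It gives the single recall as the reason for secondary status, and imprecision explains that equally well. The claim that recall error leaves the corrected slope unbiased also requires that error to be independent of the FFQ, which is open to question because both are self-reports.
- **Use is unknown.** The documents do not show whether calibrated intakes were produced, or whether this is only a slip of wording.

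None of this makes the sentence right. It is an explicit analysis rule, it conflicts with the formula just above it, and secondary status does not correct the direction.

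**Conclusion.** The definition of λ and the calibration formula do not match: the regression direction is reversed. Carried out as written, λ is off by the factor Var(FFQ)/Var(24-HR) wherever the two variances differ. The size and direction cannot be found from the documents. Over assumed 24-HR/FFQ SD ratios from 0.8 to 2.0, the factor runs from 1.56 down to 0.25.

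The conclusion rests on least-squares algebra and on reading the sentence by the convention its own section uses. Any effect on the dietary scores is conditional on scoring rules that the plan does not give. This is a clear error worth correcting, but of limited weight, because it lies within the secondary calibrated analyses of Protocol 2.

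**What to change.** Replace the definition with: *λ is the slope from linear regression of 24-HR intake (dependent) on FFQ intake (independent).* Nothing else in the formula needs to change, and the correction does not require fitting λ separately by country or sex.

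Then check the direction of the regression in any calibration code. If it follows the current sentence, recompute the calibrated intakes and the scores built on them. If it already regresses 24-HR on FFQ, or if calibration was never run, no results change.

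The cost is one sentence and a code check, plus a rerun of the calibrated secondary analyses only if the code proves to be reversed.
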